# Assessing the effect of hyperbaric oxygen therapy in breast cancer patients with late radiation toxicity (HONEY trial): a trial protocol using a trial within a cohort design

**DOI:** 10.1186/s13063-020-04869-z

**Published:** 2020-11-27

**Keywords:** Breast cancer, Radiotherapy, Hyperbaric oxygen therapy, Late toxicity, Trials within cohorts, Patient-reported outcomes

## Abstract

**Background:**

Breast cancer treatment with radiotherapy can induce late radiation toxicity, characterized by pain, fibrosis, edema, impaired arm mobility, and poor cosmetic outcome. Hyperbaric oxygen therapy (HBOT) has been proposed as treatment for late radiation toxicity; however, high-level evidence of effectiveness is lacking. As HBOT is standard treatment and reimbursed by insurers, performing classic randomized controlled trials is difficult. The “Hyperbaric OxygeN therapy on brEast cancer patients with late radiation toxicity” (HONEY) trial aims to evaluate the effectiveness of HBOT on late radiation toxicity in breast cancer patients using the trial within cohorts (TwiCs) design.

**Methods:**

The HONEY trial will be conducted within the Utrecht cohort for Multiple BREast cancer intervention studies and Long-term evaluation (UMBRELLA). Within UMBRELLA, breast cancer patients referred for radiotherapy to the University Medical Centre Utrecht are eligible for inclusion. Patients consent to collection of clinical data and patient-reported outcomes and provide broad consent for randomization into future intervention studies. Patients who meet the HONEY in- and exclusion criteria (participation ≥ 12 months in UMBRELLA, moderate/severe breast or chest wall pain, completed primary breast cancer treatment except hormonal treatment, no prior treatment with HBOT, no contraindications for HBOT, no clinical signs of metastatic or recurrent disease) will be randomized to HBOT or control group on a 2:1 ratio (*n* = 120). Patients in the control group will not be informed about participation in the trial. Patients in the intervention arm will undergo 30–40 HBOT treatment sessions in a high pressure chamber (2.4 atmospheres absolute) where they inhale 100% oxygen through a mask. Cohort outcome measures (i.e., physical outcomes, quality of life, fatigue, and cosmetic satisfaction) of the HBOT group will be compared to the control group at 3 months follow-up.

**Discussion:**

This pragmatic trial within the UMBELLA cohort was designed to evaluate the effectiveness of HBOT on late radiation toxicity in breast cancer patients using the TwiCs design. Use of the TwiCs design is expected to address issues encountered in classic randomized controlled trials, such as contamination (i.e., HBOT in the control group) and disappointment bias, and generate information about acceptability of HBOT.

**Trial registration:**

ClinicalTrials.gov. NCT04193722. Registered on 10 December 2019.

**Supplementary information:**

The online version contains supplementary material available at 10.1186/s13063-020-04869-z.

## Background

With increasing incidence and survival of breast cancer, and the therefore growing number of breast cancer survivors, long-term outcomes and side effects after breast cancer and breast cancer treatment have become increasingly important [1]. In most parts of the world, radiotherapy is part of the multimodality treatment of breast cancer in the majority of patients [1]. Radiotherapy reduces the risk of local recurrence and improves disease-free survival [2, 3]. However, it may also induce late radiation toxicity, including breast or chest wall pain, fibrosis, edema, impaired arm mobility, and decreased cosmetic outcome at least 12 months after radiation treatment.

One of the proposed treatment options for late radiation toxicity in breast cancer patients can be hyperbaric oxygen therapy (HBOT). HBOT induces neovascularization and stimulates collagen formation by fibroblasts [4]. Although HBOT is currently used in the treatment of late radiation toxicity in the breast and reimbursed by insurers, evidence of clinical effectiveness is limited [5, 6]. Also, HBOT has several side effects, such as (transient) myopia (12.8%), fatigue (14.0%), barotrauma (i.e., problems with clearing the ears due to the high pressure) (15.1%), or oxygen toxicity (0.003–1.7%) [5, 7, 8]. Oxygen toxicity is characterized by seizures, which will resolve after removal from the hyperbaric tank. Patients suffer from no additional consequences due to the oxygen toxicity and might even finish the other HBOT sessions [8]. Several small, non-randomized studies with limited follow-up have suggested a beneficial effect of HBOT in breast cancer patients, especially in terms of pain and arm mobility [5, 6].

Conducting randomized controlled trials (RCTs) with HBOT is challenging. First, patients with severe complaints may, when asked to participate in an RCT, refrain from participation because they do not want to be randomized to the control arm [9]. Also, participants might drop out after being randomized to the control arm, and obtain HBOT at their own initiative. An alternative trial design to overcome these issues is the trials within cohorts (TwiCs) design [10]. In TwiCs, the trial is nested in a prospective cohort study with regular outcome measurements. Eligible patients meeting the trial-specific inclusion criteria will be randomized to an intervention group or control group. Patients allocated to the intervention group will then be offered the intervention. The control group will not be informed about the trial. By using the cohort outcome measurements, outcomes in the intervention group are compared to outcomes in the control group.

In this study, we use the TwiCs design to investigate the effectiveness of hyperbaric oxygen therapy in comparison to usual care in breast cancer patients with late radiation toxicity.

## Methods

### Study design

This study will be performed within the UMBRELLA cohort [11]. In the prospective UMBRELLA cohort, all breast cancer patients referred for radiotherapy to the University Medical Centre Utrecht are eligible for inclusion. Currently, over 3300 patients are included and inclusion is ongoing. Upon inclusion, patients consent for (re)use of their clinical data and collection of patient-reported outcomes (PROMs) and they provide broad consent for randomization into future intervention studies [12].

The HONEY study follows the TwiCs design [10]. Within the UMBRELLA cohort, eligible patients (i.e., patients with late radiation toxicity), who consented for future randomization, will be identified as a sub-cohort for the HONEY trial. Patients from this sub-cohort will be randomized in a 2:1 ratio. Afterwards, patients allocated to the intervention arm will be offered HBOT, which they can accept or refuse (Fig. 1). Patients who refuse HBOT will receive usual care, but remain in the intervention arm. Patients who were allocated to the control arm will receive usual care and will not be informed about the trial. Their outcomes will be collected within the standard follow-up of the UMBRELLA cohort.

**Fig. 1 Fig1:**
[figure not shown]
Design of the UMBRELLA HONEY trial; a trial within cohorts design (TwiCs design), figure adapted from Relton et al. [10]

Patients with late radiation toxicity will be eligible for participation in the HONEY trial. In order to identify patients with late radiation toxicity, a self-developed late radiation toxicity questionnaire will be sent out to UMBRELLA participants who are > 12 months after the last radiotherapy fraction. The late radiation toxicity questionnaire consists of questions from different validated questionnaires. Breast and chest wall pain, social functioning, and other breast symptoms will be assessed with questions from the European Organisation for Research and Treatment of Cancer Quality of Life Questionnaire C30 (EORTC QLQ-C30), the breast-specific questionnaire EORTC QLQ-BR23, and Common Terminology Criteria for Adverse Events [13, 14]. In addition, specific questions were added by the researchers to assess possible late radiation toxicity in further detail and to evaluate eligibility criteria for the HONEY trial.

Eligibility criteria include self-reported breast pain or chest wall pain score in the late radiation toxicity questionnaire of 3 or 4 (on a scale of 1 to 4) and completed primary treatment for breast cancer (except endocrine treatment). Patients are ineligible when they were previously treated with HBOT, have contraindications for HBOT (e.g., (severe) COPD/asthma, pacemaker, morbid obesity, epilepsy in medical history, severe heart failure), and have current metastatic disease or recurrent breast cancer or when they are poor responders to UMBRELLA questionnaires (i.e., return of ≤ 2 questionnaires).

### Randomization and informed consent

In addition to the primary endpoints, other effects for the patients receiving hyperbaric oxygen therapy (i.e., tissue oxygenation, side effects of HBOT, physician-reported outcomes) will be important to evaluate. As a large effect was assumed, the sample size needed to demonstrate a significant effect was rather small. Therefore, in order to be able to answer secondary research questions, a 2:1 ratio for HBOT vs. control group randomization was applied to increase the size of the intervention arm.

A computer-generated randomization list with varying block sizes (*n* = 3–6) will be generated by an independent data manager prior to the first inclusion. Randomization will be stratified for time since inclusion in the UMBRELLA cohort (i.e., ≤ 2.5 years or > 2.5 years after start radiotherapy). The randomization list is linked to a specially designed inclusion database in Microsoft Access. The investigator has no access to the randomization list. After enrolment in the inclusion database, Microsoft Access will allocate patients to their respective treatment.

In accordance with the TwiCs design, patients randomized to the HBOT arm will be contacted by the investigator and offered to undergo HBO treatment. If they agree, they sign a second informed consent form in addition to the previously signed informed consent form of the cohort. Also, patients have the option to consent for the use of their clinical data for other studies on the same subject. In case patients drop out after providing informed consent, patients are asked for permission for the use of their clinical data in the trial. This trial does not involve collecting biological specimens for storage. The informed consent form is available from the corresponding author upon request. Patients who refuse the offer to undergo HBOT will receive treatment as usual, i.e., standard follow-up. Standard follow-up may entail physiotherapy, edema therapy, and/or analgesics, depending on the patient’s needs. Patients who are allocated to the control arm will not be informed about the HONEY trial, and undergo standard follow-up. For logistic reasons and planning of HBOT, patients will be recruited in batches (Fig. 2). After confirmation of diagnosis by a radiation oncologist, patients provide informed consent and will be referred for hyperbaric oxygen therapy.

**Fig. 2 Fig2:**
[figure not shown]
Schedule of enrollment, interventions, and assessments in the HONEY study

### Hyperbaric oxygen therapy group

The combination of high pressure and 100% oxygen inhalation induces neovascularization and regeneration in the irradiated (hypoxic) tissue [4]. During HBOT, patients are seated in a hyperbaric chamber in which the pressure will be raised from 1.0 atmospheres absolute (ATA) to 2.4 ATA. Subsequently, 100% oxygen is given through a mask placed over nose and mouth for 20 min. One treatment session of HBOT is divided into 4 parts of maximum 20 min during which patients inhale 100% oxygen. In between these parts, there are small breaks without a mask, to decrease the risk on oxygen toxicity. After the oxygen sessions, the pressure will be decreased to 1.0 ATA.

To make sure patients are eligible for hyperbaric oxygen therapy, patients will be seen by a hyperbaric oxygen therapy physician. If patients are not “fit to dive” (e.g., in case of a respiratory tract infection) in between HBOT sessions or prior to HBOT, the HBO physician might decide to cancel a HBOT session to ensure patients’ safety. In case of missed HBO sessions, the HBO physician will decide whether effectivity of HBOT is endangered. Depending on judgment of the hyperbaric oxygen physician, the HBOT might be canceled or prolonged at the end.

HBOT consists of 30–40 hyperbaric oxygen sessions (i.e., one session of 2 h per day, 5 days/week). There are appointments with the HBO physician scheduled after 15 and after 30 HBO sessions, since the first effects of HBOT on late radiation toxicity will occur after 20–30 HBO sessions. Therefore, the patient and the HBO physician will decide together whether or not an additional 10 sessions will be valuable after 30 HBO sessions, depending on the effects achieved with HBOT so far. In between hyperbaric oxygen sessions, patients in the intervention group might still require edema therapy and physiotherapy or use analgesics (i.e., usual care). All concomitant care is permitted; the use of these treatments will be monitored.

### Control group

The patients randomized to the control group will not be notified about the UMBRELLA HONEY trial and will receive usual care. As usual care entails many different treatment options, including HBOT, patients in the control group will be monitored to evaluate the treatment they undergo for the late radiation toxicity.

### Primary and secondary endpoints

The primary endpoint of this study is the difference in proportion of patients with severe/moderate reported breast/chest wall pain between both groups at 3 months follow-up (Fig. 2). Upon inclusion, all patients will have moderate/severe pain, as this is an inclusion criterion. Self-reported pain is assessed through the late radiation toxicity questionnaire on a 4-point Likert scale (i.e., none/mild/moderate/severe). Self-reported pain is dichotomized into none/mild pain and moderate/severe pain.

Secondary endpoints include physical functioning, QoL, cosmetic outcome, physician-reported pain and radiation toxicity, tissue oxygenation, and side effects of HBOT. Physical functioning will be evaluated using the late radiation toxicity questionnaire, containing questionnaires on breast and arm edema, arm mobility, and breast fibrosis. QoL will be assessed by means of the EORTC QLQ-C30 and breast-specific questionnaire EORTC QLQ-BR23 [13]. In the UMBRELLA cohort, QoL is measured upon inclusion (before start radiotherapy), at 3 months, and every 6 months afterwards. Self-reported cosmetic outcome will be assessed using the BREAST-Q questionnaire [15, 16]. Depending on previous surgery, patients fill out a different module (mastectomy/breast conserving therapy/reconstruction) yearly within the UMBRELLA cohort. Side effects will be monitored using the MacFie classification [17].

### Additional measurements intervention group

Patients included in the intervention arm, who accepted to undergo HBOT, will visit the UMC Utrecht prior to the start of HBOT and 3 months after the last hyperbaric oxygen session (Fig. 2). The first visit is a combined visit to obtain informed consent, perform physical examination by a radiation oncologist to confirm diagnosis, and obtain a standardized digital photo for cosmetic outcome.

Physical examination includes breast and/or chest wall examination to assess the extent of baseline toxicity edema and fibrosis according to the Common Terminology Criteria for Adverse Events (CTCAE) version 4.03 [14]. The Patient and Observer Scar Assessment Scale (POSAS) will be used as a scar rating scale [18]. The extent of impaired arm mobility will also be assessed. Upon inclusion, auscultation of the heart and lungs and an ear exam will be performed to assess eligibility for HBOT.

Three months after the last hyperbaric oxygen session, patients will visit the UMC Utrecht again for physical examination and a medical photo.

#### Transcutaneous oxygen measurement

Shortly prior to the HBOT, transcutaneous oxygen measurement (TCOM) will be performed and repeated 3 months after the last HBOT session (Fig. 2). TCOM is a local and non-invasive measurement [19]. With 2–4 sensors on the skin, the diffused oxygen in the skin is measured. The temperature in the sensor is slightly increased during measurement, inducing vasodilatation. Oxygenation of tissue with late radiation toxicity will be compared before and after HBOT, and to the contralateral breast without late radiation toxicity.

#### Medical photograph

A medical photograph will be taken prior to the first HBOT session and 3 months after the last HBOT session. This digital photo will be judged by expert physicians (with different medical backgrounds) to assess cosmetic outcome. These physicians will be blinded for the moment the digital photo was taken (i.e., prior or after HBOT). In addition, the symmetry of the breast (in case of breast conserving surgery or breast reconstruction) will be assessed by the BCCT.core program [20].

### Data management and trial monitoring

Every 3 months, the trial proceeding is evaluated by the trial steering group. The trial steering group consists of the principal investigator, study coordinator, and supervising staff members of the UMC Utrecht. Daily coordination, recruitment of subjects, and inclusion of trial subjects are the responsibility of the study coordinator.

In addition, study progress and data management are evaluated by an independent trial monitor.

The trial monitor evaluates adherence of the data management plan, protocol adherence, and trial progress prior to the start of the trial, after inclusion of 5 patients, and yearly afterwards. At the end of the trial (i.e., after the last patient had the last visit to the UMC Utrecht), a closing visit will be scheduled. The data management plan encompasses detailed information on data collection and storage (Additional file 1). The independent trial monitor will report outcomes of the monitoring to the institutional review board. A Data Monitoring Committee was not considered as HBOT is a low-risk intervention. The trial sponsor played no part in the study design, writing of the report, or decision to submit the report for publication. Also, the trial sponsor will not play a part in the collection of data, study management, and data analysis.

Aggregated results of the trial will be reported to all UMBRELLA patients after analysis through the annual newsletter. No post-trial care is scheduled, as no long-term harm of HBOT is anticipated. During the trial, the physicians of trial patients will be informed about the participation. Trial results will be published after analysis. Any data required to support the trial protocol as well as trial data can be supplied by the corresponding author upon reasonable request.

### Sample size considerations

Since moderate/severe pain is an inclusion criteria, all patients will have moderate or severe pain upon inclusion. We assume that 3 months after the last hyperbaric oxygen session, the proportion of patients treated with HBOT suffering from moderate to severe pain will decrease to 30% [5]. Both control patients and patients who refuse HBOT will receive usual care. It is not expected that the offer of HBOT will influence the outcome at follow-up. Consequently, we assume that of the patients receiving usual care, at least 80% will be reporting moderate/severe pain at the same time point.

It is expected that 50% of the women in the HBOT arm, who will be offered HBOT, will accept and undergo the treatment. As such, in the intervention arm, the overall proportion of women reporting moderate to severe pain will be 55% (0.5 × 30% + 0.5 × 80%) and 80% in the control group. In line with the TwiCs design, the control patients are not informed about the HBO treatment. Consequently, there will be no refusal in the control arm.

The purpose of this study is to evaluate if HBOT is either similar or better than usual care. Therefore, a directional (i.e., one-sided) test will be used. To demonstrate a significant difference of 55% vs. 80% with a power of 80%, a one-sided alpha of 0.05, and an inclusion ratio of HBOT vs. control group of 2:1, we need 72 patients in the HBOT arm and 36 patients in the control group. However, drop-out might be expected. These are not patients who refuse participation, but drop-out for other reasons, such as patients who no longer wish to participate in the UMBRELLA cohort or patients who accept the offer of HBOT, but drop-out afterwards. In order to adjust for 10% drop-out, a total of 120 (80:40) patients will be enrolled in the UMBRELLA HONEY trial. Enrollment is expected to take 20 months.

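### The purpose is given as similar-or-better and is the only reason for a one-sided test, but the design is a superiority design that can support better and never similar

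*Protocol article*

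**What the plan says.** The protocol article, Sample size considerations, states the aim in one sentence: "The purpose of this study is to evaluate if HBOT is either similar or better than usual care". The next sentence draws the consequence: "Therefore, a directional (i.e., one-sided) test will be used". No other reason for a one-sided test is given.

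The same paragraph then sizes the trial for a difference: "To demonstrate a significant difference of 55% vs. 80" per cent, with 80% power, "a one-sided alpha of 0.05" and "an inclusion ratio of HBOT vs. control group of 2:1". The result is 72 and 36 patients, raised to 80 and 40 for 10% drop-out. The 55% rests on an uptake assumption: "It is expected that 50% of the women in the HBOT arm, who will be offered HBOT, will accept and undergo the treatment". Those treated are put at 30% and those who refuse at 80%, the same as controls.

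Primary and secondary endpoints defines the endpoint as a between-group difference in the proportion with moderate or severe pain at 3 months. Data analysis compares pain response by a chi-square test. The only threshold in that section is a P value below 0.05, and no side is stated. The Abstract, Background and Discussion describe the aim as evaluating effectiveness or efficacy. The article states no non-inferiority or equivalence margin.

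**The concern.** Showing that a treatment is similar or better means ruling out that it is worse by more than a stated amount. That takes a margin and a test against it. A one-sided test of no difference has two outcomes: evidence that HBOT is better, or no such evidence. The second does not establish similarity. So the purpose sentence does not justify the test drawn from it, and it names a conclusion that the design cannot reach.

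Two things are at stake. First, with this sentence on record, a significant result reads as better and a non-significant one can be read as similar, so either could be presented as meeting the purpose. HBOT is already reimbursed on evidence that the Background calls limited, so that reading would matter. Second, the sentence is the sole support for the one-sided test, which makes a material difference to power. The side is not repeated in Data analysis, where a chi-square P value is non-directional unless someone says how to make it directional.

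**Working it through.** **Inputs, all from Sample size considerations:** control 80%; intervention arm 0.5 × 30% + 0.5 × 80% = 55%; one-sided alpha 0.05; power 80%; allocation 2:1; 72 + 36 patients; 10% drop-out.

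**1. The plan's own figure.** As a superiority comparison of two proportions:
- pooled formula, one-sided: 66 + 33 = 99; with continuity correction 76 + 38 = 114;
- exact one-sided Fisher test: 74 + 37 = 111 gives 79.9% power, and 72 + 36 gives 78.4%;
- unpooled formula, two-sided: (1.960 + 0.842)² × (0.16 + 0.2475/2) / 0.25² = 35.6, so 36 controls and 72 HBOT, an exact match.

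Drop-out: 72/0.9 = 80 and 36/0.9 = 40. The figure comes out, to within a few patients, as a superiority size. No margin enters it.

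**2. Precision if the arms are equal (80% each).**
- 72:36: SE = √[0.16 × (1/72 + 1/36)] = 0.0816; half-width 1.96 × 0.0816 = 0.160.
- 80:40: SE = 0.0775; half-width 0.152.

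**3. What a non-significant result can contain.** Control 29/36 = 80.6%, HBOT 47/72 = 65.3%. The difference is 15.3 points in favour of HBOT, 95% CI from 32.3 points better to 1.7 points worse. Pooled proportion 76/108 = 0.704, SE 0.0932, z = 1.64, one-sided p = 0.051.

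Pooled one-sided power at 72:36 is 29% for a true 10-point benefit and 48% for 15 points. At 50% uptake, a 15-point intention-to-treat benefit is 15/0.5 = 30 points among those treated. Even then a non-significant result has probability 1 − 0.48 = 0.52.

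**4. The harm side.** With untreated pain at 80%, those treated can worsen by at most 100 − 80 = 20 points. With 50% uptake and refusers unchanged, the intention-to-treat harm is at most 0.5 × 20 = 10 points.

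**5. What a similarity claim would need.** The article gives no margin, so margins of 5 and 10 points are assumptions for illustration. Both rates are 80%, one-sided alpha 0.05, power 80%, 2:1.
- Controls = (1.645 + 0.842)² × (0.16 + 0.16/2) / margin².
- 10 points: 149 + 298 = 447. 5 points: 594 + 1188 = 1782.
- Power of 72:36 for the same claim: Φ(0.10/0.0816 − 1.645) = 34%, and 15% for 5 points.

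Margins of 15 and 20 points would need 198 and 114 patients, but by step 4 they exceed the largest harm possible on the protocol's assumptions, so passing them would show little.

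**6. Why the side must be settled.** For 55% vs 80% at 72:36, pooled proportion (0.55 × 72 + 0.80 × 36)/108 = 0.633; SE under the null 0.0984; SE under the alternative 0.0888.
- One-sided 0.05: (0.25 − 1.645 × 0.0984)/0.0888 = 0.99, power 84%.
- Two-sided 0.05: (0.25 − 1.960 × 0.0984)/0.0888 = 0.64, power 74%.

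At 29/36 vs 46/72 the one-sided p is 0.038, while an ordinary chi-square P is twice that, 0.076. The two sections, each read literally, disagree on whether that result is significant.

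**The case against.** The best defence is that this is one loosely worded sentence in a consistent superiority trial. It says the study will evaluate whether, not show that, and it serves to introduce the direction of the test: the null is no difference, the alternative is better, and worse is thought implausible. On that view the article never adopts a non-inferiority design and cannot be faulted for lacking its parts. This largely stands. A reader might infer a non-inferiority trial with its margin forgotten, but the aim, endpoint, test and sizing elsewhere do not support that.

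A reader might also infer that the investigators intend to report a null result as similarity. Nothing in the article says so, and rules for wording a null result are often left to the analysis plan. The point is only that the stated purpose invites that reading.

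A third tempting inference is that the interval is symmetric, so that a null result would be compatible with 16 points of harm, or 16/0.5 = 32 points among those treated. The arithmetic is right, but step 4 caps true harm at about 10 and 20 points. Nor do the side effects listed in the Background (myopia 12.8%, fatigue 14.0%, barotrauma 15.1%) bear on the pain test; side effects are a separate secondary endpoint.

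What the defence does not rescue is the reasoning from purpose to test. If the intended meaning is superiority, the sentence should say so, and the one-sided test needs a reason of its own.

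**Conclusion.** The point holds as a mismatch between the stated purpose and the design. The trial can support better; it cannot support similar. Its main limit is that it cannot rule out worthwhile benefit: a half-width of about 16 points at 72:36 (15 at 80:40), and an observed 15-point advantage that still misses one-sided significance. The choice of side is worth about 10 percentage points of power (84% against 74%, pooled formula) and currently rests on a reason that does not support it.

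These figures assume 80% pain in controls and refusers, 50% uptake, complete data at 72:36 and no HBOT in controls. The article puts usual-care pain at 80% or more, so the 10-point harm cap is an upper bound at that uptake; higher uptake would raise it. A reader might conclude that the sample size is wrong. This point does not show that, since the stated numbers are close to what a superiority calculation gives.

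**What to change.** 1. In Sample size considerations, restate the purpose as testing whether offering HBOT is superior to usual care on moderate or severe pain at 3 months, and remove the reference to similarity.
2. Settle the side of the test identically there and in Data analysis. Either keep one-sided 0.05, give a reason that fits a superiority question and say how the chi-square P value is made one-sided (for example, halved when the difference favours HBOT); or use a two-sided 0.05 test and restate the power, about 74% at 72:36 for 55% vs 80% by the pooled formula. Removing the rationale while leaving the one-sided alpha in place would only make the side less clear.
3. Report the risk difference with its two-sided 95% CI whatever the P value, and make no similarity claim from a non-significant result.

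The changes are to wording and, at most, to the stated power. The enrolment of 120 need not change for this point. The sponsor gives up a similarity claim that the design could not support and, under the two-sided option, states a lower power.
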